## Abstract

**Background:**

About 40% of patients who have had COVID-19 still have symptoms three months later whereas a 10% may experience physical and/or psychological consequences two years later. Therefore, it is necessary to perform preventive interventions when patients are discharged from the hospital to decrease the aforementioned sequelae. The purpose of this pilot-controlled trial will be to determine the efficacy of a rehabilitation program on functional status and psychosocial factors for post-COVID-19 patients when it is delivered through a tele-care platform versus a booklet-based rehabilitation.

**Methods:**

The estimated sample size will be of 50 participants who have been discharged after COVID-19 and have a level of fatigue equal or greater than 4 on the Fatigue Severity Scale. The primary outcome will be the severity of fatigue. Participants will be randomly allocated to an “asynchronous telerehabilitation group” or to a “booklet-based rehabilitation group”. Treatment in both groups will be the same and will consist of a combination of therapeutic exercise and an educative program. Treatment outcomes will be evaluated the last day of the intervention and at three- and six-months follow-up.

**Discussion:**

The telerehabilitation intervention appears to be a viable and efficacy option in decreasing severe fatigue and other fitness variables such as strength and aerobic capacity, similar to other traditional rehabilitation formats such as through an explanatory booklet.

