## Introduction

About 40%-70% of patients still have symptoms three months later whereas a 10% may experience physical and/or psychological consequences two years later [1–3]. In addition, it is known that patients who have been hospitalized or home-bound have greater physical consequences [4]. Therefore, these symptoms can be perpetuated over time and may lead to long-term consequences called “post-COVID condition” in approximately 10% of post-COVID-19 patients [2, 5].

Fever, cough, generalized pain, gastrointestinal disturbances, dyspnea, and fatigue are amongst the most frequent symptoms in the acute phase [6]. In the post-COVID-19 phase, when the infection has disappeared, the most common symptom was fatigue, which was present from 46 to 53% of the cases [1–3].

Furthermore, psychosocial factors such as the experience of illness and isolation, have entailed to higher levels of depression, stress and anxiety in post-COVID-19 patients affecting their health and recovery [7–10]. Both, physical and psychological sequelae affect quality of life, increasing the risk of comorbidities, and slowing down the recovery of these patients [11]. This might be very detrimental, especially in the elderly population [12, 13].

So, it is necessary to perform early interventions based on therapeutic exercise to prevent and improve all these sequelae after post-acute phase [4, 14–16]. This may lead to improvements in the functional status, which ultimately may reduce dyspnea, fatigue and other associated symptoms [17], even for patients with respiratory disease [18]. However, the health system overload due to the high number of people affected, the avoidance of face-to-face attendance, and the difficulty to provide health services due to the dispersion of the population, may limit the access of people to treatment after hospital discharge.

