#### Control group

The BRG will perform the same therapeutic exercise and education program than the ATG but through a booklet-based rehabilitation, which will include key pictures and descriptions for every exercise of each level. In addition, patients in the BRG will receive the same therapeutic education recommendations that in the ATG but in text format.

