#### Sample size calculation

A sample size of 50 subjects will be required, 20 in each group, plus 10 in anticipation of future losses according to the recommendations for RCT pilot studies [95, 96].

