#### Statistical analysis

Statistical analysis will be performed with Statistical Package for the Social Sciences version 25.0 (SPSS Inc, Chicago, IL). The significance level will be 0.05 for all statistical analyses. Descriptive statistics, including frequency counts for categorical variables and measurements of central tendency and dispersion for continuous variables (standard deviation, 95% confidence interval) will be calculated to summarize the data.

The Shapiro-Wilk test will be used to determine the normality of the data.

General lineal models will be performed to compare the intervention effects [time (pre-intervention vs post-intervention vs follow-up 1 and 2 assessments) x group interaction] on the primary and secondary outcomes: severity of fatigue, functional status, self-efficacy, depression, anxiety and stress, quality of live, behavioral regulation in sport and perceived social support. It will be examined with analysis of variance (ANOVA) mixed model for repeated measures when normal distribution will be detected. A post hoc test will be used to locate the differences between the groups, if necessary. If data are not normally distributed, statistical analysis will be performed using non-parametric correspondent tests like Friedman test to compare the three moments involved and Wilcoxon test if statistics significance will be reached in previous Friedman test. In Wilcoxon test, type I error will be divided by the number of tests done.

For the aerobic capacity, strength, functional status post-COVID and feasibility outcomes, comparisons between-groups outcomes will be using t-tests for independent samples and Levene test for parametric data, or Mann-Whitney test U tests for non-parametric data. Chi-square and Fisher tests will be used of independence for categorical data. Finally, in the event of possible dropouts, analyses will be conducted as intention to treat.

Between- and within-group effect sizes using Cohen’s d or r for main outcomes will also be computed.

Chi square test for qualitative data and t-test or Mann-Whitney for normal or not normal data respectively will be used to check the comparability between the two groups at baseline.

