## Discussion

This protocol describes a pilot and feasibility study to analyze the efficacy of an exercise and education therapeutic program using asynchronous telerehabilitation for post-COVID-19 patients. The aim of the pilot study will be to analyze if there are improvements in the participants´ level of fatigue and if these changes are maintained in the short (3 months) and medium term (6 months) and compare it with traditional home rehabilitation using a booklet. The secondary aim will be to analyze the feasibility of this pilot study.

Telerehabilitation is well accepted in terms of overall user experience, adherence, and satisfaction [94]. So, it represents a great opportunity for the treatment and monitoring of long-term patients. Currently, the large increase of COVID-19 cases during 2020 and 2021 has made telerehabilitation-based consultation a viable and reliable option in several pathologies. Scientific evidence shows how telerehabilitation is already effective in post-COVID-19 patients, as reported in the systematic review of da Silva et al. [97] where it was found that a physical programme using telerehabilitation can improve functional capacity, dyspnea and quality of life. Similarly, Dalbosco-Salas et al. [98], found that a group of post-COVID-19 patients undergo remote rehabilitation using synchronous telerehabilitation, achieved improvements in physical condition and quality of life. Although their model is on-line and there is no control group, the study shows positive results for post-COVID-19 patients in lower limb strength and quality of life. Furthermore, in most of the studies carried out in the acute and post-COVID-19 patients, the control group does not receive treatment.

Moreover, telerehabilitation has also shown to be effective in many other different conditions such as musculoskeletal pain, chronic obstructive pulmonary disease (COPD) or cardiovascular disease [99]. The study of Lewis et al. [100] showed that telerehabilitation is effective in COPD patients on multiple variables such as lower limb strength, fatigue, dyspnea, and anxiety, including improvements also in patient engagement and exercise progression. Similar results were obtained by Batalik et al. [101], who performed a study with asynchronous telerehabilitation in cardiac patients and showed also to be effective to improve the aerobic capacity assessed with the 200 meter fast-walk test.

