When telerehabilitation is compared to other formats, most of the studies about telerehabilitation reported clinical improvements in favor of telerehabilitation, but no statistically significant changes compared to other ways, which leads us to expect similar results in our study. Suso-Martí et al. [102] in their systematic review with meta-analysis, showed how telerehabilitation generated clinical improvements in physical condition variables in cardiorespiratory, musculoskeletal, and neurological patients, even comparable to conventional face-to-face rehabilitation. Other studies such as Dias et al. or Hansen et al. [103, 104] reported how telerehabilitation was not different to other interventions for physical function. The systematic review of Dias et al. [103] concluded that exercise via telerehabilitation can be an alternative to improve physical function and quality of live in persons with disabilities. Moreover, Hansen et al. [104] also found how telerehabilitation was similar to face-to-face rehabilitation in severe COPD patients to improve the aerobic capacity and the lower limb strength.

Regarding the psychosocial factors, several trials, such as ours, have implemented in their protocols a therapeutic education program together with the exercise program, with the aim of improving the emotional components by telerehabilitation [105]. These interventions seem to show better results than those based on isolated therapeutic exercise [103, 106]. However, although it seems that emotional factors can be improved with therapeutic education, it has no effect on decreasing the perception of fatigue [107]. In the cross-sectional study by Milani et al. [108] in adult population with a physical disability, it was observed that those patients who were able to undergo synchronous telerehabilitation via Skype had higher self-efficacy with respect to the control group. In addition, Hansen et al. [104] demonstrated improvements in the depression scale, compared to the group without telerehabilitation, measured with the HADS-D scale.

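### The abstract's message that telerehabilitation reduces severe fatigue and is similar to the booklet cannot be supported by a small two-format pilot that plans only difference tests

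*Protocol article*

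**What the plan says.** The abstract's Discussion paragraph calls telerehabilitation an efficacious option for decreasing severe fatigue, and describes it as "similar to other traditional rehabilitation formats such as through an explanatory booklet". The article's Discussion gives the background to that expectation: earlier comparisons of formats found "no statistically significant changes compared to other ways, which leads us to expect similar results in our study".

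The first paragraph of the Discussion states the aim as whether there are improvements in the participants' "level of fatigue and if these changes are maintained in the short (3 months) and medium term (6 months"; the same sentence goes on to a comparison with the booklet. Feasibility is named there as the secondary aim.

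Under Statistical analysis, "The significance level will be 0.05 for all statistical analyses". The methods listed are a time-by-group model, t-tests and their non-parametric counterparts. No equivalence or non-inferiority hypothesis or margin appears. The section also plans "Between- and within-group effect sizes using" Cohen's d or r.

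On size: "A sample size of 50 subjects will be required, 20 in each group, plus 10 in anticipation of future losses", justified by recommendations for pilot trials. On treatment: "The BRG will perform the same therapeutic exercise and education program than the ATG", differing only in format. Entry requires an FSS score of at least 4 (Eligibility criteria), and FSS is the primary outcome.

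**The concern.** Two claims are attached to this trial, and each needs evidence that the design does not produce.

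- **Similarity of the two formats.** A difference test that does not reject says only that the data are compatible with no difference. Similarity requires an interval narrow enough to exclude differences that matter.
- **Efficacy of the programme against fatigue.** That requires a comparison with patients who did not receive the programme. Here both arms receive it.

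The result that the authors seem to expect is that both arms improve with no significant difference between them. Read through the abstract's wording, it would support both claims. Yet it would also fit spontaneous recovery in both arms together with a moderate true difference between formats in either direction. A service could then replace one format with the other on evidence that does not bear on the question.

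**Working it through.** **Inputs from the protocol.** Significance level 0.05 (taken as two-sided; the text does not say); 1:1 allocation; 20 per arm after the allowed losses, or 25 per arm if nobody is lost. No SD, target difference, power or margin is given, so results are in SD units. Pre-post correlations r are assumptions.

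**The plan's own figure.** 2 × 20 + 10 = 50. It reproduces, and uses no target precision or margin.

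**Precision.** The 95% half-width for a difference in means at one assessment is t(0.975, 2n−2) × √(2/n).

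- 20 per arm: 2.024 × √(2/20) = 0.64 SD
- 25 per arm: 2.011 × √(2/25) = 0.57 SD

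Baseline adjustment multiplies this by √(1−r²). A change-score contrast, which is what a time-by-group interaction tests between two assessments, multiplies it by √(2(1−r)).

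| 95% half-width (SD) | 20 per arm | 25 per arm |
|---|---|---|
| Unadjusted | 0.64 | 0.57 |
| Change score, r = 0.5 | 0.64 | 0.57 |
| Change score, r = 0.6 | 0.57 | 0.51 |
| Change score, r = 0.7 | 0.50 | 0.44 |
| Baseline-adjusted, r = 0.6 | 0.51 | 0.45 |
| Baseline-adjusted, r = 0.7 | 0.46 | 0.41 |

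If the FSS SD were 0.8 to 1.5 points (assumed), 0.64 SD is 0.51 to 0.96 points. The protocol's own severity levels are about one point apart.

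**Power of the difference test.** For a true difference of 0.5 SD, from the noncentral t distribution with noncentrality 0.5 × √(n/2) and no adjustment: 34% with 20 per arm and 41% with 25. A difference of that size would therefore be non-significant 66% or 59% of the time.

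**What a similarity claim would need.** Taking 0.5 SD purely as an illustrative margin, with a true difference of zero and two one-sided tests at 0.05, unadjusted power is 3% with 20 per arm and 10% with 25. For 80% power, the size per arm is 2 × [(1.645 + 1.282)/0.5]² = 68.5, so 69. For a margin of 0.3 SD it is 191.

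**What within-arm change can show.** No arithmetic settles this; three statements do, side by side.

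1. The Intervention and Control group sections give both arms the same exercise and education, so the randomised contrast is app against booklet.
2. The Introduction says: "About 40%-70% of patients still have symptoms three months later whereas a 10% may experience physical and/or psychological consequences two years later". The two percentages do not measure the same thing, but they point towards recovery over time in COVID-19 patients generally.
3. Patients are selected for a high value of the primary outcome, so some fall on re-measurement is expected without any treatment effect.

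A fall in FSS within an arm therefore mixes programme effect, recovery and regression to the mean, and nothing in the design separates them.

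**The case against.** **The plan never says that p>0.05 will be reported as equivalence.** Correct. A reader might infer such a rule, but none is written. The abstract sentence is hedged, the Discussion behind it mainly reviews other studies, and the expectation of similar results can be read as expecting results like theirs. What remains is that the sentence stands as the abstract's discussion of this trial and names its comparator and primary outcome, while the body text ties the expectation to this study on the strength of non-significant differences elsewhere.

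**The booklet is the right comparator.** It is, for a question about delivery format, and identical content isolates that question. A reader might infer that the lack of an untreated arm is a design error. It is not; it only limits what may be claimed. Nor does the plan say that within-group effect sizes will serve as proof of efficacy.

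**A pilot may be small, and its report may be more careful than its abstract.** The sample size is not criticised here. A margin could sit in an analysis plan that is not shown, but the stated sample size and tests do not use one.

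**The figures can be pushed too far.** One might say that a 0.5 SD margin is missed even when the observed difference is zero. That holds only for an unadjusted comparison with 20 per arm, where the 90% half-width is 0.53 SD. With 25 per arm it is 0.47 SD. With 20 per arm and r = 0.6 it is about 0.48 SD for a change score and 0.43 SD with baseline adjustment. Likewise, the size of regression to the mean cannot be derived: the population mean, SD and retest correlation are not given, and it is unclear whether the screening FSS is also the baseline FSS. The prevalence figures in the Introduction are not FSS courses in patients hospitalised for more than five days.

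**Conclusion.** The abstract's claims of efficacy against severe fatigue and of similarity to the booklet are wrong as written for this design, and the improvement-and-maintenance part of the Discussion aim needs qualification. A non-significant FSS result would be inconclusive: unadjusted, the interval extends about 0.57 to 0.64 SD either side of the estimate, and about 0.4 to 0.5 SD with baseline adjustment at r = 0.6 to 0.7. Unadjusted power against 0.5 SD is about 34% to 41%. These figures assume two-sided testing, 20 to 25 analysed per arm and a common SD; the correlations and the 0.5 SD benchmark are assumptions. Improvement within an arm cannot be attributed to the programme. Recovery and regression to the mean are plausible explanations, but their size cannot be stated from the protocol. The fault lies in what the trial is said to show; the choice of arms and the pilot sample size stand.

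**What to change.** - **Abstract, Discussion paragraph:** remove the efficacy and similarity claims. State instead that the trial estimates the difference between two delivery formats and assesses feasibility.
- **Statistical analysis:** state that the primary result is the between-arm FSS difference with its 95% confidence interval; that p>0.05 alone is reported as inconclusive; and that similarity is claimed only if the interval lies inside a margin written down and justified before analysis. If no margin is set, make no similarity claim.
- **Discussion, statement of aims:** reword so that within-arm change, its maintenance at three and six months and within-group effect sizes are descriptive, and say that they are not evidence that the programme works.

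The cost is wording and a more modest claim. Arms, sample size, assessments and data collection stay as they are. The observed SD and pre-post correlation can then be used to size a later trial if similarity is the real question.

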**Clinical trial registration:**

This trial has been prospectively registered at clinialtrials.gov identifier: NCT04794036.

## Introduction

About 40%-70% of patients still have symptoms three months later whereas a 10% may experience physical and/or psychological consequences two years later [1–3]. In addition, it is known that patients who have been hospitalized or home-bound have greater physical consequences [4]. Therefore, these symptoms can be perpetuated over time and may lead to long-term consequences called “post-COVID condition” in approximately 10% of post-COVID-19 patients [2, 5].

Fever, cough, generalized pain, gastrointestinal disturbances, dyspnea, and fatigue are amongst the most frequent symptoms in the acute phase [6]. In the post-COVID-19 phase, when the infection has disappeared, the most common symptom was fatigue, which was present from 46 to 53% of the cases [1–3].

Furthermore, psychosocial factors such as the experience of illness and isolation, have entailed to higher levels of depression, stress and anxiety in post-COVID-19 patients affecting their health and recovery [7–10]. Both, physical and psychological sequelae affect quality of life, increasing the risk of comorbidities, and slowing down the recovery of these patients [11]. This might be very detrimental, especially in the elderly population [12, 13].

So, it is necessary to perform early interventions based on therapeutic exercise to prevent and improve all these sequelae after post-acute phase [4, 14–16]. This may lead to improvements in the functional status, which ultimately may reduce dyspnea, fatigue and other associated symptoms [17], even for patients with respiratory disease [18]. However, the health system overload due to the high number of people affected, the avoidance of face-to-face attendance, and the difficulty to provide health services due to the dispersion of the population, may limit the access of people to treatment after hospital discharge.

The use of telerehabilitation, defined as the delivery of rehabilitation services via technologies, appears to be a viable option [4, 13]. Furthermore, it could reduce the possible consequences of disease and prevent disability without the need to attend in person [12, 14, 19]. In addition, asynchronous telerehabilitation allows to incorporate home-based rehabilitation for the treatment of patients who have been discharged and do not require face-to-face treatment. This benefits especially to different population groups such as those who live in rural areas and has less access to health services, who experience any mobility limitations or have to be confined at their homes [20, 21].

According to the current scientific evidence, the efficacy of telerehabilitation has been demonstrated in many other pathologies such as the cardiac, neurological, respiratory, and musculoskeletal [19, 22–26]. There is already evidence of the efficacy of telerehabilitation interventions in the acute phase of COVID-19, at hospital setting patients and at home setting patients without hospitalization [27–30]. On the other hand, several studies have shown that telerehabilitation interventions can lead to an increased patient adherence and satisfaction [24, 31, 32]. To the authors’ knowledge, no previous studies have assessed if an asynchronous telerehabilitation program consisting of a combined therapeutic exercise and education program is effective to improve the functional status and the patient´s adherence and satisfaction of post-COVID-19 patients.

Therefore, the aim of this pilot study will be to analyze the efficacy on fatigue, functional status and psychosocial factors of a 12-weeks therapeutic exercise and education program, when this is delivered through an asynchronous telerehabilitation format versus a booklet-based rehabilitation format in post-COVID-19 patients.

## Methods

### Study design

This protocol will be a pilot and feasibility study with a single-blind randomized clinical trial design. The trial has been designed according to the Standard Protocol Items: Recommendations for Interventional Trials (SPIRIT) and will compare two parallel interventions: an intervention group (asynchronous telerehabilitation group, (ATG)) and a control group (booklet-based rehabilitation group, (BRG)). The duration of the study will be 12 months, with 12 weeks of intervention and two follow-ups at three- and six-months post-intervention. Figs 1 and 2 illustrate the pilot trial design. The study protocol has been approved by the Ethics Committee of Aragón (reference number: PI21/019, current protocol version date April 04, 2021). The protocol has been registered at clinialtrials.gov (NCT04794036).

